# Exploring the effects of a combined exercise programme on pain and fatigue outcomes in people with systemic sclerosis: study protocol for a large European multi-centre randomised controlled trial

**DOI:** 10.1186/s13063-022-06853-1

**Published:** 2022-11-28

**Keywords:** Systemic sclerosis, Pain, Fatigue, Exercise, High-intensity interval training, Microvascular function, Quality of life, Aerobic, Muscular function

## Abstract

**Background:**

Pain, related to Raynaud’s phenomenon or digital ulceration, has been identified as very prevalent and debilitating symptoms of systemic sclerosis (SSc), both significantly affecting patients’ quality of life (QoL). Pharmacological therapeutic strategies were found not to be sufficiently effective in the management of SSc-induced pain and fatigue, and evidence for exercise is scarce. As yet, the effects of a long-term, tailored exercise programme on pain and fatigue in patients with SSc have not been explored. In addition to pain and fatigue, this study aims to evaluate the effects of exercise on QoL, physical fitness, functional capacity, and vascular structure in people with SSc (PwSSc).

**Methods:**

This will be a multicentre (*n* = 6) randomised controlled clinical trial to assess the effect of a previously established, supervised 12-week combined exercise programme on pain and fatigue as compared to no exercise in PwSSc. The study will recruit 180 patients with SSc that will be allocated randomly to two groups. Group A will perform the exercise programme parallel to standard usual care and group B will receive usual care alone. Patients in the exercise group will undertake two, 45-min sessions each week consisting of 30-min high-intensity interval training (HIIT) (30-s 100% peak power output/30-s passive recovery) on an arm crank ergometer and 15 min of upper body circuit resistance training. Patients will be assessed before as well as at 3 and 6 months following randomisation. Primary outcomes of the study will be pain and fatigue assessed via questionnaires. Secondary outcomes include quality of life, structure of digital microvasculature, body composition, physical fitness, and functional capacity.

**Discussion:**

Data from this multi-centre research clinical trial will primarily be used to establish the effectiveness of a combined exercise protocol to improve pain and fatigue in SSc. In parallel, this study will be the first to explore the effects of long-term exercise on potential microvascular alterations assessed via NVC. Overall, this study will provide sufficient data to inform current clinical practice guidelines and may lead to an improvement of QoL for patients with SSc.

**Trial registration:**

ClinicalTrials.gov NCT05234671. Registered on 14 January 2022

**Supplementary Information:**

The online version contains supplementary material available at 10.1186/s13063-022-06853-1.

## Background

Systemic sclerosis (SSc) is a rare autoimmune disease of unknown aetiology characterised by skin fibrosis and internal organ and vascular involvement. SSc is more common to women compared to men with a ratio of almost 5:1 to be consistently reported in the majority of studies [1]. Geographically, the incidence and prevalence of SSc varies across Europe. More specifically, a North-South gradient in Europe has been previously proposed [2] with Northern European countries such as the UK, Finland, and Iceland presenting lower rates compared to Southern European countries such as France and Greece.

Pain and fatigue [3] are two of the most common and important patient-reported outcomes in rheumatology [3] and SSc [4]. Several organ systems and factors are responsible for the origination of both pain (e.g. vascular, dermal, musculoskeletal, gastrointestinal, genitourinary) and fatigue (e.g. cardiac, respiratory, muscular, systemic inflammation, psychological, neurological, malnutrition, sleep-related, and medication-related) [4]. Both symptoms (i.e. pain and fatigue) are strongly linked to poor quality of life (QoL) in people with SSc [4].

Pharmacological therapeutic strategies [5] have been adopted in the management of pain and fatigue in SSc without being sufficiently effective [6–8]. The evidence of the effectiveness of non-pharmacological interventions (e.g. the effects of exercise on SSc pain and fatigue) is limited [9, 10], but promising [11–15]. Engagement in regular exercise is associated with lower pain intensity and interference in people with SSc [16] (PwSSc). Higher daily physical activity levels are associated with improved skin microvascular function in type 2 diabetes [17] (a clinical condition with increased vasculopathy similar to that observed in SSc). This might explain partly why RP’s severity (i.e. pain) and presence of ulcers are observed less in toes (as lower limbs are the most commonly used body part for daily activities) when compared to fingers [18].

Physically active PwSSc have lower levels of fatigue compared to inactive individuals [16]. Moreover, evidence (e.g. one-to-one semi-structured interviews) from our recently completed feasibility study [12] suggests that PwSSc feel more energetic and stronger following a combined (e.g. aerobic and resistance training) exercise programme, also improving their fitness and social life [12]. Thus, a feasible, safe, long-term exercise programme for PwSSc that will improve pain and fatigue is warranted. Therefore, and being supported by published evidence [12–14], the aim of the current European randomised controlled clinical trial (RCT) is to assess the effect of such an exercise programme primarily on pain and fatigue, as well as on QoL, physical fitness, upper body functional capacity, and digital vascular structure in PwSSc.

## Methods

### Study design

The CESPF (The effects of a combined supervised exercise programme on pain and fatigue in SSc) study is a multi-centre (*n*=6) randomised (1:1 ratio), parallel group, superiority, controlled clinical trial. One hundred and eighty SSc will be recruited across six research institutions (Sheffield Hallam University, Sheffield, UK; Karolinska Institutet, Stockholm, Sweden; Rigshospitalet Hospital, Copenhagen, Denmark; Leiden University Medical Center, Leiden, Netherlands; Aristotle University, Thessaloniki, Greece; University of Campania L. Vanvitelli, Naples, Italy) and will be randomly assigned via stratified block randomisation remotely by an independent statistician to either group A (combined exercise) or group B (control group). Both groups will continue receiving their usual medical as well as non-pharmacological treatment (if applicable) throughout the study. Patients will be followed for 6 months following randomisation (Fig. 1). Assessors will be blinded regarding the allocated treatments. The study’s protocol and registration have been published in ClinicalTrials.gov (NCT number: NCT05234671) January 02, 2022. The trial is sponsored by the Foundation for Research in Rheumatology, and medical (where applicable) or non-medical ethical approval has been granted by each research centre locally. The reporting of this study protocol is done according to the Standard Protocol Items Recommendations for Interventional trials (SPIRIT).

**Fig. 1 Fig1:**
[figure not shown]
Study design. VAS-SHAQ, Visual Analogue Scale-Scleroderma Health Assessment Questionnaire; FACIT-F, functional assessment of chronic illness therapy—fatigue; SScQoL, Systemic Sclerosis Quality of Life Questionnaire; CES-D, Centre for Epidemiologic Studies Depression Scale; NVC, nailfold videocapillaroscopy

### Recruitment of participants

The RCT will recruit 180 (exercise group *n* = 90 and control group *n* = 90) PwSSc from the above-mentioned six European study/recruitment centres via local rheumatological clinics. PwSSc who meet the eligibility criteria (see below) and express an interest will receive a detailed patient’s information sheet from the treating health care professional (e.g. rheumatologist, physiotherapist, nurse). Following a certain time period dependant on each country’s ethical regulations, a study investigator will contact them either via letter or telephone to address any queries regarding the study and arrange an initial appointment. Clinical care will not be affected for those not wishing to take part or withdraw from the study. Depending on the conditions of local ethical approvals, at the first visit, participants will be familiarised with the study’s procedures, provide informed consent, and complete baseline assessments. Informed consent will be performed by the local designated principal investigator.

### Eligibility criteria

Patients eligible for the trial must comply with all the following inclusion and exclusion criteria:

#### Inclusion criteria

A diagnosis of SSc according to the 2013 American College of Rheumatology/European League Against Rheumatism criteria and experiencing RPAge over 18 years oldAbility to perform the prescribed exercise regime

#### Exclusion criteria

Active disease-related exacerbations (e.g. active digital ulcers)Change of medical vascular function-related treatment (i.e. vasodilators) within the last 3 monthsAdvanced pulmonary involvement (e.g. pulmonary arterial hypertension)New York Heart Association class 3 or 4Inability to exerciseCurrent pregnancy

### Group randomisation

Following VISIT 1, participants will be randomised remotely (to ensure allocation and concealment) into groups A (combined exercise) and B (control group), using a computer programme (nQuery Advisor 6.0, Statistical Solutions, Ireland) to generate stratified block-randomisation (by research centre, SSc-type, disease duration and severity), by an independent statistician. Each participant will be allocated a unique trial number across all sites (e.g. SSc001) that will remain with them throughout the study.

### Exercise intervention

The exercise intervention will require patients to be randomly allocated into two groups. Groups A and B will serve as the exercise and control groups, respectively. The comparison between those who will perform an individualised combined (aerobic and resistance training) exercise programme with supervised sessions and those who will not perform the exercise programme is essential to examine whether exercise is beneficial and effective for PwSSc.

Following randomisation, group A will perform a 12-week combined exercise programme (aerobic and resistance training) twice per week. The exercise programme will be performed adjunctive to usual care. Each session will be supervised and will consist of 3- to 5-min warm up performing light to moderate intensity arm cranking (55–65% of peak power output; PPO), 30-min high-intensity interval training (HIIT; 30 s at 100% of PPO and 30-s passive recovery) and 3 to 5 min of cool down period (40–50% of PPO) on an arm crank ergometer. The PPO will be individualised tested when performing the peak exercise test on an arm crank ergometer at baseline assessments (see assessments section). The HIIT protocol will be combined with resistance training (RT) lasting for a total of approximately 15 min. RT will be consisted of an upper body circuit training (five exercises): (1) shoulder lateral raise in a sitting position with dumbbells, (2) chest press on a bench in a 30° supine position with dumbbells or chest press machine, (3) biceps curl in a sitting position with dumbbells, (4) triceps extension in a sitting position with dumbbell or standing position in a pulley machine with straight grip, and (5) hand squeeze of a handgrip dynamometer, for three circuits. The intensity for all the exercises except the handgrip dynamometer will be at 75–80% of one repetition maximum (1-RM; that will be determined indirectly via validated 1-RM prediction formulas [19]) performing 10 repetitions of each exercise interspersed by 20–30 s to allow for safe movement between exercises. For the handgrip dynamometer exercise, the intensity will be maximum for 10 repetitions. The recovery period between circuits will last 2–3 min. Following each exercise session, patients will undertake a 5-min cool-down period, involving arm cranking (e.g. corresponding to “light intensity” based on rating of perceived exertion; RPE [20]) and some light stretching with focus on pectoral and deltoid muscles (3–4 repetitions to each arm for 20–30 seconds). Heart rate (HR; using a heart rate monitor chest strap) and RPE will be monitored at regular intervals (both during the exercising bouts as well as during the passive recovery approximately every 5 min) throughout the exercise session. Blood pressure (BP) will be monitored pre- and post- each session. A qualified health care professional (e.g. clinical exercise physiologist/physical therapist with experience in SSc) will supervise the exercise session.

Any potential adverse events (e.g. pain) during the exercise sessions will be assessed for relation with the intervention and will be recorded by the health care professional.

### Control group

Group B will not perform any exercise intervention and will only receive the usual care. To assure the provision of equal opportunities for both groups, following VISIT 3 (e.g. meaning the completion of the research protocol for the participants), group B will be offered the same exercise intervention as in group A.

### Withdrawals

Patients will be considered as withdrawn from the research trial if they request to leave the trial if they are lost to follow-up or if they die before completing the 6-month follow-up. Discontinuation of the allocated intervention will be applied in case of adverse events that may compromise patient’s health status or reduce health related QoL.

#### Six pillars of adherence

The 6 pillars of adherence will be used to support the feasibility, recruitment, and participation enjoyment levels of PwSSc. This approach has been successfully applied in our research group’s previous clinical trials with PwSSc [12, 21], developing thus a standard quality service.

“Social support”: Participants are encouraged to speak to family members if they wish to, and if the implemented health protocols allow it, they can bring a friend or family member together with them at assessments. Research has showed that those who receive support to continue from a member of their inner circle are usually the ones who complete treatments successfully.

“Education”: Participants are educated for the benefits of exercise and healthy diet. The focus lies primarily on the overall health and wellbeing benefits, explaining also in lay terms that recent work suggests that there is a clinical outcome potential (fewer digital ulcers and hospitalisations) [13].

“Reachability”: Reachability is the ascertaining to participants of easy and quick contact (i.e. phone, email, social media) to provide them valuable support. This allows study’s participants to reach the research team outside the exercise sessions with questions, queries, and advice requests.

“Small groups intervention implementation”: Wherever that is possible (i.e. depending on available training equipment) small groups are formed, where the same people on each session, exercise together, supporting each other, trying to create a social element supporting thus adherence to exercise training.

“Reminders”: Apart from the initial provision of a detailed programme, participants receive reminders of their upcoming sessions via e-mail and/or text, at least one day before their exercise sessions.

“Simplicity”: The fitness goals are kept simple, realistic, and individualised based on individualised exercise testing. Participants are receiving appropriate education of the importance to set simple attainable goals.

### Assessments

Assessments will be performed at baseline (i.e. VISIT 1), at 3 months (i.e. VISIT 2) and at 6 months (i.e. VISIT 3). Assessments will consist of questionnaires and physical tests. All physical tests are administered by trained assessors, who are blinded to the patients’ randomisation status. To ensure high-quality standards of the proposed assessments, the study’s research manager (AM) will provide across centres a common standard operation procedure (SOP) digital manual for all baseline measurements (including follow-up visits), as well as day-to-day quality monitoring procedures.

### Outcomes

#### Primary outcomes

##### Pain (overall and digital)

Overall pain will be assessed using the VAS-SHAQ (Additional file 1) [22]. VAS-SHAQ is consisted of a 15-cm which is converted to a continuous scale from 0 to 3 (1cm = 0.2 points on the VAS). Digital pain will be assessed using a unidimensional measure of pain intensity, which has been widely used in diverse adult populations, including those with rheumatic diseases [23]. The pain VAS will be comprised of a horizontal line,100 mm in length, anchored by 2 verbal descriptors, one for each symptom extreme: “no pain” (score of 0) and “worst imaginable pain” (score of 100) [23]. For both VAS-SHAQ and digital VAS scales, participants will be requested to self-complete the pain by placing a line perpendicular to the VAS line at the point that represents their overall and digital pain intensity, respectively.

#### Secondary outcomes

##### Quality of life

SSc-related QoL will be assessed using the SScQoL questionnaire [26] (Additional file 3), and the CES-D (Additional file 4) [27] will be used to assess the depressive symptoms. The SScQoL is a questionnaire comprising 29 questions exploring the impact of SSc on health and well-being, covering four themes identified by PwSSc: emotion, physical adaptation, impact on/with others, and impact on self.

The Centre for Epidemiologic Studies Depression Scale (CES-D) has shown to be a reliable and valid measure of depressive symptoms in patients with SSc [28]. The CES-D is a 20-item measure, with the frequency of each depressive symptom rated on a 4-point Likert scale ranging from 0 to 3 (“rarely or none of the time” to “most or all of the time”).

##### Digital cutaneous microvascular structure

NVC will be performed using an optical probe (200× contact lenses) connected to image analysis software. Images will be observed on a high-resolution colour monitor. Patients will be instructed to wash their hands gently with an antibacterial soap, and following 15 min of rest (i.e. seated), NVC will be performed at a standardised room temperature of 20–25°C. The nailfolds of six digits (e.g. index, middle, and ring in both hands) will be examined in each patient, and a drop of vegetable oil will be placed on the nailfold bed to improve the image resolution. Digits that will be affected by severe local trauma will not be analysed. The following parameters will be recorded and analysed: scleroderma patterns (e.g. early, active, late), presence of enlarged and giant capillaries, haemorrhages, loss of capillaries, disorganisation of the vascular array, and ramified/bushy capillaries [29]. A qualitative and semi-quantitative scoring of SSc patterns by NVC will be performed as described and validated previously [30, 31].

Prior to NVC assessment, patients will be instructed to avoid from caffeine and smoking for at least 4 h and to not remove the fingernail cuticles for at least 2–3 weeks to avoid microtraumas that could affect the examination.

### Peak oxygen uptake test

Throughout the test, gas exchange will be collected and analysed by an online breath-by-breath analysis system. Heart rate (HR) and the electrocardiogram (ECG) will be continuously monitored. RPE (6–20 points [20]) will be recorded during the last 10 s of every minute during the exercise test until volitional exhaustion. Blood pressure will be assessed prior and 5 min following the termination of the exercise test to assure resting values have been reached. Peak power output (PPO) measured in watts and test duration (e.g. minutes) will be recorded. Peak oxygen uptake (V̇O_2peak_) will be defined as the average oxygen during the last 30s. The incremental exercise protocol will be calculated based on patient’s physical activity levels. Physical activity is assessed via certain questions (e.g. regular physical activities or exercise training, duration of each session, intensity, and mode of exercise) concerning the last 4 weeks. The crank rate will be maintained above 50 rev min^−1^ (patient’s will be allowed to select and maintain their own comfortable crank rate), and power requirements will be increased as a linear ramp at a rate of 10 W/min and 6 W/min for males and females, respectively [32, 33]. The test will be commenced with 2 min collecting resting values and 3 min of warm-up (unloaded cranking). RPE ≥18 and/or inability to maintain a crank rate above 50 rev min^-1^ will be resulted in the termination of the test. After the exercise termination, an unloaded or very low loaded (e.g. <5watts) bout of 2–3 min exercise at a crank rate below 40 rev min^−1^ will follow to allow for an active recovery period.

### Handgrip test

Southampton protocol for adult grip strength measurement will be utilised [34], and participants will be familiarised with procedures prior to testing. The participant will be seated in a standard chair with legs, back support, and fixed arms. The same chair will be utilised for every measurement. The forearms will be placed on the arms of the chair with the wrist just over the end of the arm of the chair (i.e. wrist in a neutral position, thumb facing upwards). Jamar handgrip dynamometer will be positioned as such so as the thumb is round one side of the handle, and the four fingers are around the other side. The assessor will rest the base of the dynamometer on the palm of their hand as the subject holds the dynamometer (to negate the effect of gravity on peak strength). The participant will be instructed to squeeze as long and as tightly as possible or until the needle stops rising. Once the needle stops rising, the participant will be instructed to stop squeezing. Strength will be reported in kilogrammes. The measurement will be repeated in the left hand. Three attempts will be performed in total for each side and the best of the three grip strength measurements will be recorded. Moreover, hand dominance (e.g. right, or left) or ambidextrous (i.e. people who can genuinely write with both hands) will also be recorded.

### Arm curl test

The aim of this test is to do as many arm curls as possible in 30 s. This test will be conducted on the dominant arm side. The participant will be seated on the chair, holding the weight in the hand with palm facing towards the body and the arm in a vertically down position beside the chair. The upper arm will be supported against the body so that only the forearm will be moving. The arm will be fully bent and then fully straightened at the elbow. The arm curl test will require the subject to repeatedly lift a 2-kg weight (for women) or a 4-kg weight (for men) for 30 s [35]. The number of lifts will be recorded.

### Clinical management

All patients in both groups will continue receiving their standard medical treatment such as calcium channel blockers (e.g. nifedipine, sildenafil) and will be reviewed in the clinic as often as is deemed clinically necessary.

Moreover, in case of adverse events or worsening of symptoms due to exercise, patients will be withdrawn from the study for health and safety reasons. Patients can also withdraw on own request.

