### Safety monitoring

We will record all serious adverse events (as defined below), as well as all non-serious adverse events that are deemed to be related to participation in the research, during the period between the provision of informed consent through to 6 months after randomisation.

Serious adverse events are defined as any untoward medical occurrence that either results in death, is life-threatening (i.e. the patient is at risk of death at the time of the event occurring), requires unplanned admissions to emergency hospitalisations or prolonged hospitalisation (deemed to be where a patient’s stay is longer than expected, e.g. patient is operated on as a day case but remains in hospital overnight) or results in persistent or significant disability or incapacitation.

A non-serious event in the context of this trial will be any untoward medical occurrence to the participant that is related to the patients’ involvement in the study but does not fulfil any of the serious adverse event criteria.

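### Two sections give conflicting rules for exercise-related adverse events; the one that removes patients from the study would lose pain and fatigue data mainly in the exercise arm

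*Protocol article*

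**What the plan says.** The protocol article deals with exercise-related harm in two places.

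- **Withdrawals:** "Patients will be considered as withdrawn from the research trial if they request to leave the trial if they are lost to follow-up". Death during the 6 months is the third ground. Adverse events are not on that list. They have a separate and lesser consequence: "Discontinuation of the allocated intervention will be applied in case of adverse events". The events meant are those that threaten the patient's health or quality of life.
- **Clinical management:** "in case of adverse events or worsening of symptoms due to exercise, patients will be withdrawn from the study for health and safety reasons". The next sentence adds that patients may also withdraw at their own request.

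Four other statements bear on the point.

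- **Exercise intervention:** "Any potential adverse events (e.g. pain) during the exercise sessions will be assessed for relation with the intervention", so pain is the article's own example of an adverse event.
- **Control group:** "Group B will not perform any exercise intervention and will only receive the usual care". The programme is offered to controls only after the last visit.
- **Study design:** "Patients will be followed for 6 months following randomisation".
- **Safety monitoring:** adverse events are recorded "during the period between the provision of informed consent through to 6 months after randomisation".

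**The concern.** The same kind of event leads to two different outcomes, and the article does not say which rule takes precedence. The difference matters because pain and fatigue are the primary outcomes and the trigger in Clinical management is close to them: worsening symptoms attributed to exercise. It will arise mainly in group A. Controls undergo exercise tests at visits but do no programme during follow-up.

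The 12-week programme ends at the primary time-point. A participant removed during training has no 12-week score, and one removed between the second and third visits has no 24-week score. Under this rule, missingness depends on the participant's own deterioration and is concentrated in one arm, so it is probably not at random. The people left in the exercise arm would look better than those randomised to it. Safety follow-up would also stop early in the participants whom exercise had harmed.

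**Working it through.** **The two rules side by side**

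| | Withdrawals | Clinical management |
|---|---|---|
| Trigger | Adverse events that may compromise health or reduce quality of life | Adverse events, or worsening symptoms due to exercise; no severity threshold |
| Consequence | Allocated intervention stops | Patient leaves the study |
| Grounds for leaving the trial | Request, loss to follow-up, death | The trigger above, and request |

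Withdrawals treats stopping treatment and leaving the trial as separate events, so Clinical management cannot easily be read as meaning only that exercise stops. It also places its rule next to withdrawal on request, which Withdrawals counts as leaving the trial. Because it has no severity threshold, it reaches milder events too.

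**Inputs for the size of the bias**

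- From the article: 90 per arm, significance level 0.05, 80% power and 15% dropout (Sample size); 12 weeks as the primary time-point (Statistical analysis).
- Assumed, because the article gives no figure: no true effect; k = 2, 5 or 9 of 90 exercise participants (2%, 6%, 10%) lost before the 12-week visit through the rule; k controls lost at random; correlation of 0.5 or 1.0 between the withdrawal trigger and the 12-week score, with 1.0 an upper bound; baseline-to-follow-up correlation of 0.5 or 0.7 for ANCOVA; two-sided test.

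Nine losses would be two-thirds of the all-cause dropout allowance: 9 / (0.15 × 90) = 9 / 13.5 = 0.67.

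**Analytic check.** Removing the worst fraction p of a standard normal score shifts the mean of those who remain by φ(z) / (1 − p), where z is the upper-p point. This is multiplied by the trigger correlation.

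- p = 5/90: shift 0.119 SD at correlation 1.0, and 0.5 × 0.119 = 0.059 SD at correlation 0.5.
- p = 9/90: shift 0.195 SD at correlation 1.0, and 0.5 × 0.195 = 0.097 SD at correlation 0.5.

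**Simulation** (50,000 trials per scenario). In each trial the k exercise participants with the highest trigger are removed. Entries are bias toward exercise in SD / two-sided type I error.

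| Lost | Trigger correlation | t-test | ANCOVA, baseline corr. 0.5 | ANCOVA, baseline corr. 0.7 |
|---|---|---|---|---|
| 2 | 0.5 | 0.027 / 5.5% | 0.021 / 5.4% | 0.013 / 5.2% |
| 2 | 1.0 | 0.051 / 6.8% | 0.039 / 6.3% | 0.028 / 6.1% |
| 5 | 0.5 | 0.058 / 6.9% | 0.043 / 6.5% | 0.029 / 5.8% |
| 5 | 1.0 | 0.118 / 13.5% | 0.091 / 11.6% | 0.063 / 9.5% |
| 9 | 0.5 | 0.096 / 9.9% | 0.073 / 8.6% | 0.050 / 7.3% |
| 9 | 1.0 | 0.191 / 27% | 0.148 / 21.4% | 0.105 / 16.7% |

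An independent repeat agreed within simulation error. The t-test biases match the analytic shifts.

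**Scale.** The article states no effect size or SD, so its sample size cannot be reproduced. Inverting it with 15% loss (90 × 0.85 = 76.5 per arm) gives a detectable difference of (1.960 + 0.842) × √(2/76.5) = 0.45 SD. For 5 lost, the t-test bias is 0.058/0.453 = 13% of that at correlation 0.5 and 0.118/0.453 = 26% at correlation 1.0. ANCOVA at correlation 0.5 stays under 10% (0.043/0.453 = 9.5%).

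Losses after the second visit affect only the 24-week value.

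**The case against.** The strongest reply is that Clinical management may simply be loosely worded. It does not say that outcome collection ends, and its stated purpose is health and safety. The dedicated Withdrawals section, the 6-month follow-up and the 6-month safety recording all point to continued follow-up. A standard operating procedure manual and protocol version 2.0 exist but are not shown, and they may settle the matter. This makes the benign reading possible, but the visible conflict remains: the literal reading is the ordinary one, and a centre could follow it in good faith.

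The second reply concerns size. No withdrawal rate is given, the article calls the intervention low risk, and the eligibility criteria exclude active exacerbations and advanced cardiopulmonary disease. The largest figures need 9 withdrawals and a perfectly correlated trigger. Pain during a session is not the same as the pain score at 12 weeks, and an early flare may have settled by then, which would weaken the link. This stands: at low rates the bias is small, and its direction depends on those withdrawn still being worse at 12 weeks.

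Third, both pain scales are marked by the participant on a line, which cannot be done by telephone. Approval is local to each centre, and recruitment was due to end by January 2023, so an amendment may come too late for some participants. These points limit the remedy but do not affect the finding.

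**Conclusion.** The concern holds. The current text contains two incompatible rules, and the one in Clinical management is wrong as written for a trial whose primary outcomes are pain and fatigue. The conflict itself is certain. The harm is conditional on centres following Clinical management and on assessments stopping at that point.

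The size is unknown. Under the stated assumptions it runs from negligible (2 lost, correlation 0.5: type I error 5.2% to 5.5%) to serious at the upper bound (9 lost, correlation 1.0: 17% to 27%). For 5 lost, the bias is 0.03 to 0.12 SD and the type I error 5.8% to 13.5%, depending on trigger correlation and analysis. Sensitivity analyses could bound the bias, but no analysis can recover questionnaires that were never collected. This should be fixed.

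**What to change.** In Clinical management, replace removal from the study with discontinuation of the exercise programme, using the same criterion as Withdrawals. State that such participants remain in the trial and complete the pain and fatigue questionnaires at the 3- and 6-month visits unless they withdraw consent. If they cannot attend, send the forms by post; the line-marked pain scales should not be taken by telephone. Continue adverse event recording to 6 months and analyse participants in the arm to which they were randomised. For anyone already removed under the present wording who has not reached 6 months, ask whether they will still complete the questionnaires.

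The cost is a one-line amendment, any local approval it needs, a reminder to six centres, and a few extra questionnaires from people who have stopped training. The sample size does not change, nor does the decision on when exercise is stopped.
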